#### 2.7.6. Conventional Fall Prevention Workshop (Intervention) (Phase 2)

The conventional-format intervention sessions will receive instructions from a professional team composed of an occupational therapist and a speech-language therapists, who will guide participants through exercise workshops focused on muscle strengthening, static and dynamic balance training, weight-shifting activities, stretching exercises, functional reaching tasks, strength training, and postural control responses, including righting, support, and balance reactions, using a traditional, non-technology-based approach.

These workshops will follow the same distribution schedule as the experimental intervention, consisting of two sessions per week, each lasting 60 min. Sessions will be structured into a warm-up phase, a main exercise phase, and a cool-down phase, with scheduled rest periods distributed between exercises; the only difference will be the modality of the exercise program. The process for both the experimental and conventional interventions is illustrated in Figure 7.

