#### 2.7.2. Pre-Intervention Assessment (Phase 1)

As part of the program implementation, a pre-intervention assessment will be conducted, focusing on the evaluation of multiple functional and perceptual components. Vestibular-related symptoms will be assessed using the Dizziness Handicap Inventory (DHI). Physical performance will be evaluated through handgrip dynamometry, while functional mobility will be assessed using the Timed Up and Go (TUG) test and the Short Physical Performance Battery (SPPB). Functional status will be measured using the Barthel Index and the Instrumental Activities of Daily Living scale by Hernández and Neumann. The psychological dimension associated with falls will be evaluated using the Falls Efficacy Scale–International (FES-I) and the Activities-specific Balance Confidence (ABC) Scale.

A maximum period of two weeks will be established for the completion of all baseline assessments. Following this period, minimum eligibility criteria for participation in the intervention will be confirmed prior to the initiation of the immersive virtual reality-based intervention.

Regardless of group allocation (control or experimental), each intervention session will follow the structured schedule described in Table 2, with a total duration of 60 min (including preparation, warm-up and cool-down phases, exercises, and rest periods). According to the Manual for Fall Prevention in Older Adults [32], sessions should focus on exercises targeting muscle strengthening, static and dynamic balance, weight-shifting activities, stretching exercises, functional reaching tasks, strength training, and postural control responses, including righting, support, and balance reactions. In addition, the intervention will be adapted according to participants’ interests, preferences, difficulty level, and individual functional profiles.

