#### 2.7.4. Virtual Reality-Based Falls Prevention Workshop (Intervention) (Phase 2)

##### VR-Based Program Implementation Sessions

The intervention sessions corresponding to the Virtual Reality Program for Older Adults in Primary Health Care (PHC), aimed at falls prevention, will be implemented in accordance with the guidelines established in the Information Guide for Therapeutic Interventions with Immersive Virtual Reality (INVIRTUE) [33]. The clinical objective of the program is to reduce fall risk and maintain functional capacity within the framework of strategies for preventing functional decline in older adults. The intervention will have a total duration of twelve weeks, with a frequency of two sessions per week and an approximate duration of 60 min per session. The process will be supervised by an interdisciplinary team composed of occupational therapists and speech-language pathologists, who will provide continuous clinical monitoring, personalized feedback, and timely management of any adverse symptoms associated with the use of immersive virtual reality (iVR), such as dizziness, nausea, or disorientation.

Prior to the initiation of the program, an introductory session will be conducted to familiarize participants with the technology. During this session, explanatory audiovisual content will be presented, information regarding the therapeutic objectives will be provided, and a practical demonstration of device use will be performed. Participants’ questions will be addressed, and potential concerns related to the immersive experience will be discussed.

For the deployment of the intervention, appropriate preparation of the physical environment will be essential, ensuring a spacious, safe area free of obstacles. During each session, the instructor will activate the device and establish the necessary connection to project the experience onto an external screen, allowing the remaining group members to observe the activity and participate interactively through verbal feedback.

Subsequently, each participant will directly engage with the immersive virtual reality environments under constant supervision by the professional team, ensuring safety conditions, therapeutic support, and systematic monitoring of intervention tolerance.

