In Balance Exercise 3, participants will receive visual stimuli, specifically lights, which they must deactivate by following a previously established pattern. This activity will prioritize lateral and anteroposterior weight shifts, controlled weight unloading, and functional reaching tasks, with the aim of promoting dynamic postural adjustments and standing balance control (Figure 4). In Balance Exercise 4, a cognitive component will be incorporated alongside movement. Each participant will be required to reach for colored balls and place them into a container that follows a specific pattern assigned to a given color (green or yellow). This task integrates functional mobility, hand–eye coordination, and cognitive processing related to color discrimination and associative matching (Figure 4).

In addition to balance and strengthening components, the intervention program will incorporate specific exercises targeting vestibular system training, including visual tracking activities, head rotations, directional changes during ambulation, body turns, and both static and dynamic balance tasks (Figure 5). These activities are designed to progressively stimulate sensory integration mechanisms and postural control processes, with the aim of optimizing stability and reducing fall risk among older adults within an immersive virtual reality environment.

Finally, all sessions will include closing exercises focused on activities of daily living (ADLs). The purpose of these activities is to facilitate the transfer of the skills trained to real-world contexts, enabling older adults to integrate and apply the competencies acquired in virtual environments to everyday situations (Figure 6).

Each of these activities will allow real-time adjustment of the number and speed of stimuli, as well as execution time, according to the individual characteristics of the participants, under the supervision of the professional team. The incorporation of these customizable features within digital applications enhances adherence to the intervention, as it enables task personalization based on goals centered on each individual’s needs and specific functional profile. Additionally, performance monitoring will be conducted in real time through tracking and feedback mechanisms integrated into the KINESIX XR^®^ system.

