#### 2.9.4. Intervention Adherence

Intervention adherence is defined as the percentage of intervention sessions effectively completed by each participant relative to the total number of sessions planned in the protocol. This indicator will be used to assess the level of compliance and active participation of participants in the intervention. Based on the study design, a minimum adherence rate of 80% is expected in both the experimental and control groups (*n* = 32).

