COOL-DOWN	5 min.	Exercises according to the Fall Prevention Manual for Older Adults and VIVIFRAIL program, with emphasis on breathing technique, flexibility, and prevention of cybersickness symptoms.
“Total active intervention time: 60 min including preparation and rest periods.”		

VIVIFRAIL: Multicomponent Physical Exercise Program; Category B: Moderate functional limitation; Category C1: Frail; Category C2: Pre-Frail; D: Autonomous; ADL: Activities of Daily Living.

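### Section 2.7.6 says the arms differ only in modality, but the protocol contradicts itself on what the control arm receives and has no measure of hands-on exercise time

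*Protocol article*

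**What the plan says.** Section 2.7.6 describes the conventional workshop as having the same frequency and session length as the experimental one, and concludes that "the only difference will be the modality of the exercise program". It gives the control content as "exercise workshops focused on muscle strengthening, static and dynamic balance training, weight-shifting activities, stretching exercises, functional reaching tasks, strength training, and postural control responses", delivered without technology.

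Section 2.7.2 says: "Regardless of group allocation (control or experimental), each intervention session will follow the structured schedule described in Table 2". Table 2 includes an 8 min vestibular row and a 5 min ADL row. It also carries a virtual reality title, opens with device adjustment and ends with a cool-down aimed partly at preventing cybersickness. Section 2.7.5 in turn presents Table 2 as the structure of the virtual reality sessions.

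Within the account of the virtual reality programme, section 2.7.5 states that "the intervention program will incorporate specific exercises targeting vestibular system training" and that "all sessions will include closing exercises focused on activities of daily living (ADLs"). It also adds a cognitive element to Balance Exercise 4. Section 2.7.4 has the instructor project the headset view on a screen, "allowing the remaining group members to observe the activity and participate interactively through verbal feedback", after which each participant uses the environment in person.

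Section 2.9.4 defines adherence as the "percentage of intervention sessions effectively completed by each participant relative to the total number of sessions planned in the protocol".

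**The concern.** H1 compares TUG between the arms, and section 2.8 uses the group-by-time term to evaluate the virtual reality intervention. The sentence in section 2.7.6 invites the reader to take any difference as an effect of modality. That reading needs the two arms to match in exercise content and in time spent exercising.

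The article gives two incompatible accounts of control content, and it describes some features for one arm only. If content or hands-on time differs, a positive TUG result could reflect the extra content, and a null result could reflect less exercise actually done in one arm. The direction of any bias is not fixed: shared use of equipment could lower active time in the virtual reality arm, while extra components could favour it. The planned adherence measure would not separate these explanations.

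**Working it through.** **Inputs (Table 2, minutes).** Set-up 3 (counted from session onset), warm-up 5, Balance 1 5, Balance 2 8, rest 3, Balance 3 8, Balance 4 5, rest 3, vestibular 8, ADL 5, cool-down 5. Sections 2.7.4 and 2.7.6 give two sessions per week, and section 2.7.4 gives twelve weeks: 2 × 12 = 24 sessions.

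**The table's own total.** 3 + 5 + 5 + 8 + 3 + 8 + 5 + 3 + 8 + 5 + 5 = 58 min, against the stated "Total active intervention time: 60 min including preparation and rest periods". The set-up row starts before session onset by an unstated time, and section 2.7.4 calls 60 min approximate, so the 2 min gap is not an established error. Labelling the total as active is loose, because it includes set-up and 6 min of rest.

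**Core exercise time.** Balance 1 to 4, vestibular and ADL: 5 + 8 + 8 + 5 + 8 + 5 = 39 min per session, or 39 × 24 / 60 = 15.6 h over the programme.

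**Vestibular plus ADL.** 8 + 5 = 13 min per session; 13 / 39 = 33% of core time; 13 × 24 / 60 = 5.2 h over the programme.

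**Difference between arms under each account:**

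| Account of control content | Vestibular and ADL in control | Difference per session | Over 24 sessions |
|---|---|---|---|
| Section 2.7.2 governs (Table 2 in both arms) | 13 min | 0 min | 0 h |
| Section 2.7.6 list is complete | 0 min | 13 of 39 min | 5.2 of 15.6 h |

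**Can both accounts hold?** Not as written. A workshop without technology cannot follow the device-adjustment step in Table 2. The mismatch also runs the other way: section 2.7.6 names strengthening for controls, and no Table 2 row names it.

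**Features described for one arm only.** The cognitive task in Balance Exercise 4 appears in section 2.7.5. The Table 2 row for Balance 4 (5 min) mentions no cognitive work, and section 2.7.6 names none. The projected-screen format in section 2.7.4 has no stated control counterpart. Neither is added to the 0 to 13 min range. The Balance 4 slot exists in both arms if Table 2 applies to both, and time spent observing cannot be calculated because neither the number of headsets nor the number of people per session is given.

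**Adherence.** The numerator and denominator in section 2.9.4 are both sessions. Two participants with the same percentage can have different hands-on minutes, and so can two arms.

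**The case against.** The strongest reply is that section 2.7.2 settles the matter: it applies Table 2 to both arms explicitly, so vestibular and ADL work belongs to both. The control list in section 2.7.6 closely repeats the general list in section 2.7.2, which also omits vestibular and ADL work although that section applies Table 2. Silence in section 2.7.6 therefore does not show that controls go without. The rest periods in section 2.7.6 also match Table 2. This stands as far as it goes. A reader might infer that vestibular and ADL work is given to the virtual reality arm alone, and the documents do not support that; they support a contradiction.

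A reader might also infer that most of each virtual reality session is spent watching, or that the delivered exercise is low. Section 2.7.4 does not say so. It says that every participant engages directly, and no figure allows the time to be worked out. Section 2.9.4 counts sessions effectively completed, which might exclude a session mostly watched, but the article does not say what the term requires.

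Further, combined motor and cognitive demand is the declared nature of the intervention, so the cognitive task can fairly be read as part of the modality. H1 concerns the intervention against control rather than modality in isolation, and section 2.1 describes preliminary effects. Allocation of pre-existing groups without randomisation (section 2.2) limits attribution in any case. These points reduce the stakes. They do not make the sentence in section 2.7.6 consistent with the rest of the article. Figure 7, not available here, may add detail on the two processes, but it would not remove the conflict between the text sections.

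**Conclusion.** The concern holds in a limited form. The statement that modality is the only difference is not supported by the article's own descriptions. The vestibular and ADL difference is unresolved, between 0 and 13 of 39 core minutes per session (0 to 33%, or 0 to 5.2 h over 24 sessions), depending on which section governs. The upper end assumes that the section 2.7.6 list is exhaustive, and the lower end that Table 2 applies in full to controls. The observing format is described for one arm only. So is the cognitive task, with the reservation that it may be part of the modality. Session-based adherence cannot show whether hands-on time was similar.

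As written, a TUG difference, or its absence, can be read only as a comparison of two programmes as delivered. The 58 against 60 min total is a minor wording point. The stated sample size is not affected.

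**What to change.** 1. Reconcile sections 2.7.2, 2.7.4, 2.7.5, 2.7.6 and Table 2 so that each arm has one stated content and schedule. Which content each arm should receive is for the investigators to decide.
2. Unless content and hands-on time are shown to be matched, replace the only-difference sentence in section 2.7.6. State instead that the comparison is the virtual reality programme against the conventional programme, each as delivered, and limit the conclusion on H1 to that.
3. Record hands-on exercise minutes per participant per session in both arms and report them beside session adherence. Section 2.7.5 already provides for real-time performance tracking in the virtual reality system, which may help in that arm; the control arm would need a simple log.
4. Reword the Table 2 footer so that set-up and rest are not labelled as active time.

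The cost is wording changes, a short session log and a narrower claim if matching cannot be shown.

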### 2.8. Statistical Analysis

Data analysis will be performed using IBM SPSS Statistics software, version 30.0. Prior to analysis, data cleaning and coding procedures will be conducted to verify the absence of errors, outliers, or missing values. All statistical analyses will be carried out using a significance level of *p* < 0.05 and a 95% confidence interval.

At an initial stage, a descriptive and exploratory analysis will be conducted to characterize the sample and examine the distribution of the study variables. Sociodemographic variables (including age, sex, educational level, and comorbidities) will be summarized using absolute and relative frequencies for categorical variables, and measures of central tendency and dispersion (mean, median, standard deviation, and interquartile range) for continuous variables. Normality will be assessed using the Shapiro–Wilk test. Based on distributional assumptions, between-group comparisons will be performed using the independent-samples *t*-test for normally distributed continuous variables, the Mann–Whitney U test for ordinal variables or continuous variables with non-normal distributions, and the chi-square test for nominal variables.

To evaluate the effects of the virtual reality intervention, a two-way repeated-measures ANOVA will be conducted to test group-by-time effects (group × time). The primary analysis will follow the intention-to-treat (ITT) principle. A minimum of 20 imputed datasets will be generated, and this number may be increased depending on the proportion of incomplete data. Effect sizes will be estimated using partial eta-squared (ηp^2^) and interpreted as small (0.01), medium (0.06), or large (0.14) [36].

To control for inflation of type I error across secondary endpoints, *p* values for the prespecified secondary outcome analyses will be adjusted using the Holm–Bonferroni sequential procedure. This method was selected because it appropriately controls the family-wise error rate in the presence of multiple comparisons while being less conservative than the traditional Bonferroni correction. The correction will be applied to the secondary outcomes FES-I, ABC, SPPB, and handgrip strength. For the primary outcome, unadjusted *p* values will be reported. For the secondary outcomes, both unadjusted and Holm-adjusted *p* values will be presented, together with effect sizes and 95% confidence intervals [37].

To control for inflation of type I error across the secondary outcomes, the Holm–Bonferroni sequential correction procedure will be applied to FES-I, ABC, SPPB, and handgrip strength [38,39]. This method was selected because it appropriately controls the family-wise error rate in the presence of multiple comparisons while being less conservative than the traditional Bonferroni correction [38,39]. For the primary outcome, unadjusted *p* values will be reported, whereas for the secondary outcomes both unadjusted and adjusted *p* values will be presented. Regarding statistical power, because the sample size was determined primarily based on the primary outcome, the secondary outcomes will be considered supportive and exploratory. With a statistical power of 80%, the study is expected to be more sensitive to large effects, whereas small effects in the secondary outcomes may not be detectable. Therefore, these findings will be interpreted with caution.

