### 2.2. Study Setting and Participants

Older adults enrolled in programs aimed at maintaining comprehensive health for older populations within the primary health care (PHC) system, particularly those affiliated with the More Self-Reliant Older Adults program (+AMA) in the city of San Pedro de la Paz, Biobío Region, Chile, will be invited to participate in the implementation of this protocol. The +AMA program is a nationwide intervention implemented by municipal health departments across Chile and is designed to promote self-reliance, self-care, and active ageing among adults aged 60 years and older [24]. The groups participating in this program comprise individuals with diverse functional levels and health conditions, including both autonomous older adults and those in a pre-frail condition or at risk of frailty, thereby allowing access to a heterogeneous and representative community-based population.

The selection of +AMA program groups and other older adult groups affiliated with PHC services is based on their operational feasibility for protocol implementation. These groups are characterized by stable organizational structures and regular participant attendance, which facilitates the delivery of the intervention. Access to participants will be managed through a collaboration agreement with the Municipal Health Department (Departamento de Salud Municipal, DAS) of San Pedro de la Paz. This agreement will define the mechanisms for coordination, dissemination, and execution of the protocol within the designated community settings, ensuring appropriate collaboration between health care teams and the implementation of the planned activities.

Allocation to experimental or control conditions will be conducted at the group level, based on pre-existing community groups. This approach aims to prevent contamination between participants, preserve the natural group structure of PHC workshops, and enhance ecological validity. Given the community-based nature of the intervention, individual randomization was not feasible. Baseline comparability between groups will be examined prior to outcome analyses.

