### 2.3. Sample Size

The sample size (*n* = 40) was calculated a priori for a mixed repeated-measures design with two groups (control vs. experimental) and two assessment time points (pre- and post-intervention). The calculation assumed a significance level of α = 0.05, a statistical power (1 − β) of 0.80, and an expected small-to-moderate effect size (f = 0.25), with an assumed within-participant correlation of 0.5 and a nonsphericity correction of ε = 1.0. Under these assumptions, a minimum of 34 participants was required, evenly distributed as 17 individuals per group. Considering the potential for participant attrition and to ensure an adequate sample for pre- and post-intervention analyses, an attrition rate of approximately 15–20% was anticipated. Therefore, a total of 40 older adults will be recruited, with 20 participants allocated to the experimental group and 20 to the control group. The flow of participants through each stage of the study will be presented using a adapted CONSORT flow diagram adapted for quasi-experimental studies (Figure 1).

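### The article's only stated response to baseline differences between its non-randomised groups is to examine them, and its effect test corrects for a stable TUG gap but not for regression to the mean or for factors that affect change

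*Protocol article*

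**What the plan says.** Section 2.2 describes the assignment: "Allocation to experimental or control conditions will be conducted at the group level, based on pre-existing community groups". It adds that "individual randomization was not feasible", and that "Baseline comparability between groups will be examined prior to outcome analyses". It does not say what follows if the groups turn out to differ.

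Section 2.8 names the effect analysis: "a two-way repeated-measures ANOVA will be conducted to test group-by-time effects (group × time"), under intention to treat with at least 20 imputed datasets. No covariate is named. The other comparisons are unadjusted too: "between-group comparisons will be performed using the independent-samples *t*-test for normally distributed continuous variables", with Mann–Whitney and chi-square tests for other variable types. Where Section 2.8 speaks of adjustment, it means the Holm correction for multiple secondary outcomes.

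Section 2.3 sizes the trial on the same interaction test, with "an expected small-to-moderate effect size (f = 0.25") and "with an assumed within-participant correlation of 0.5 and a nonsphericity correction of ε = 1.0", which leads to 34 participants, raised to 40.

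Table 1 requires a TUG of 10 to 20 s at entry. Section 2.7.2 measures TUG in the baseline assessment and confirms eligibility afterwards, so the screening value also serves as the baseline value.

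**The concern.** Confounding is the main threat to a comparison of intact, self-formed groups, and Section 2.2 itself describes the source population as mixed in function and health. The planned test protects against one kind of difference, a constant gap in TUG. Two kinds remain.

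- **Regression to the mean.** Participants enter on a TUG window, and the qualifying measurement is the baseline. If one group starts slower and part of that is transient, it will appear to improve more.
- **Factors that affect change.** Age, sex, comorbidity and baseline function may influence how much a person gains over 12 weeks. All are collected (Sections 2.7.2 and 2.8), but none enters the model.

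At stake is H1, a between-group claim tested at 0.05. If adjustment is not fixed in advance, any adjustment made later will be chosen after the imbalance has been seen.

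**Working it through.** **1. The plan's own figure.** Inputs from Section 2.3: α = 0.05, f = 0.25, ρ = 0.5, ε = 1.0, two groups, two times. For the interaction, λ = N·m·f²/(1 − ρ) with m = 2 and df (1, N − 2). At N = 34, λ = 34 × 2 × 0.0625/0.5 = 8.5 and power is 0.807. At N = 32 power is 0.781. The stated minimum of 34 is reproduced.

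**2. What that test is.** In a 2 × 2 mixed design the interaction F equals the squared two-sample t on change scores (checked on a generated data set: both 0.9617). The variance of change is 2(1 − ρ)σ² = 1.0σ². Setting N·D²/(4 × 1.0) = 8.5 with N = 34 gives D = 1.0 SD. So the trial is sized to detect a difference in mean change of one SD, with no covariates.

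**3. Assumed inputs.** The article gives neither a TUG SD nor an expected imbalance. Let the true baseline difference d be 0.25 to 1.0 SD, with no intervention effect and 20 per group.

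**4. Case A: both groups regress to a common mean.** The expected spurious difference in change is (1 − ρ)d. Rejection rates of the nominal 5% test:

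| d (SD) | Bias at ρ = 0.5 (SD) | Change-score test, ρ = 0.5 | Change-score test, ρ = 0.8 | Baseline-adjusted regression |
|---|---|---|---|---|
| 0.25 | 0.125 | 6.7% | 5.7% | 5.0% |
| 0.50 | 0.25 | 12.0% | 7.7% | 5.0% |
| 0.75 | 0.375 | 21.1% | 11.4% | 5.0% |
| 1.00 | 0.50 | 34.0% | 16.7% | 5.0% |

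At d = 0.5 SD and ρ = 0.5, the spurious 0.25 SD is a quarter of the planned 1.0 SD effect.

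**5. Case B: the baseline gap is stable (parallel trends).** The change-score test holds 5.0% throughout. Baseline-adjusted regression now carries a bias of d − ρd = (1 − ρ)d. At ρ = 0.5 it rejects 7.2%, 13.8%, 23.5% and 34.7% of the time for the same four values of d.

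**6. Would examining comparability catch it?** For a t-test at 20 per group, λ = N·d²/4 = 40 × 0.25/4 = 2.5 at d = 0.5 SD, which gives power 0.338. It misses that imbalance about two times in three. Larger gaps are flagged more often: 64% at 0.75 SD and 87% at 1.0 SD.

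**7. Precision.** The residual variance after baseline adjustment is (1 − ρ²)σ² = 0.75σ². At 17 per group, power for D = 1.0 SD would be 0.903 against 0.807. That figure assumes balanced baselines, no further covariates and no clustering. If success required both tests to be significant, simulation (20,000 trials, 17 per group) gives about 0.79, and 0.76 to 0.77 with three uninformative covariates added.

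**The case against.** The strongest reply is that the planned test does use baseline TUG. A change score subtracts each person's own starting value, so a lasting difference between community groups drops out. Intact groups may well differ in just that way, and then the planned test is valid and baseline-adjusted regression is the biased method (step 5). The documents do not say which case applies. This stands. A reader might infer that the plan ignores baseline TUG, or that regression on baseline should simply replace the ANOVA; neither inference is supported.

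Three further replies also stand in part.

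- Both groups share the same entry windows and receive supervised exercise on the same schedule. This limits confounding but does not remove it.
- A reader might infer that the interaction cannot be pooled over imputed datasets. It has one degree of freedom and equals a difference in mean change, which pools directly. Only partial eta-squared is awkward, and that is minor.
- The precision gain to 0.90 should not be promised, since it assumes the balance that is in doubt.

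It can also be said that covariate lists and sensitivity analyses belong in an analysis plan that is not shown, and that the trial aims only at preliminary effects. That would hold if the article were silent on the model. It names the model, sizes the trial on it, and tests a between-group hypothesis with it.

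**Conclusion.** The point holds in limited form. As written, the plan leaves regression to the mean and confounders of change uncorrected in a non-randomised comparison. Its one stated check has 34% power against a 0.5 SD imbalance and leads to no stated action.

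The possible harm is a type I error of about 7% to 34%. That range rests on an assumed imbalance of 0.25 to 1.0 SD, the plan's ρ = 0.5, and regression to a common mean. At ρ = 0.8 it is about 6% to 17%. If group differences are stable, the planned test stays at 5%.

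The defect is therefore not that the wrong one of two estimators was chosen. It is that a single estimator is reported, with its assumption unstated, where two defensible ones can disagree.

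Neither analysis can separate the intervention from the group effect if each arm is a single community group; the article does not state how many there are.

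**What to change.** In Section 2.8, for TUG and each secondary outcome:

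- Pre-specify a regression of the post-intervention value on arm, the baseline value of that outcome and a short fixed list of covariates already collected (for example age, sex and baseline SPPB), pooled over the imputed datasets.
- Report its estimate and 95% CI beside the group × time result.
- State the assumption behind each: stable group differences for the change score; for the regression, no remaining group difference given baseline and covariates.
- Describe a conclusion that differs between the two as not robust to baseline differences.

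In Section 2.2, describe comparability by standardised differences, and say that baseline p values will not decide whether to adjust.

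Do not make formal agreement of both tests the success rule. At 17 per group that gives about 0.79 power, or about 0.76 with three uninformative covariates, below the stated 0.80.

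The cost is a few degrees of freedom and one extra table, with no new data and no further participants.
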